# VI. PATIENT SELECTION

### A. Patient population

A total of 36 eligible patients will be required to complete this protocol. Broadly, eligible patients will be asymptomatic HIV infected individuals with a CD4+ cell count of at least 350 cells/mm3.

### B. Inclusion criteria

Patients must fulfill all of the following inclusion criteria to be eligible for therapy,

a) documented HIV-1 infection (positive HIV-ELISA and confirmatory test by one of several methods).

b) 18 years old or greater.

c) a single CD4+ cell count of at least 350 cells/mm3 within 30 days prior to randomisation (to be conducted by central laboratory -Appendix G).

d) the following clinical laboratories must be observed within 30 days of randomisation:

i. serum AST < 4.9 times upper limit of normal range (ULN) for the study site

ii. serum bilirubin < 2 x ULN

iii serum creatinine < 2.0 mg/dl

iv granulocyte count > 1000 cells/ mm3

v. hemoglobin > 11.0 g/dl

vi. platelet count > 50000 cells/mm3

e) a Karnofsky Performance Status > 80 (appendix A).

f) women of childbearing potential must provide a negative serum or urine pregnancy test within 14 days prior to randomization.

g) men and women should employ best available barrier contraception at all times.

h) patients should provide written informed consent that conforms to local, national and international requirements for the protection of human subjects in medical research.

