#### 3. Pre-cycle IL-2 (day 1/cycle 1) - Patients randomized to IL-2

This visit must occur within 96 hours of commencement of IL-2, for IL-2 therapy. The following tests must be completed and the results known to be in keeping with study eligibility criteria before the patient is treated with IL-2:

- physical examination, vital signs and Karnofsky Performance Status
- CBC, differential and chemistries
- urinalysis
- urine or serum pregnancy test for women of childbearing potential
- flow cytometry panel
- whole blood for PBMC processing/storage

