**Table 3**

**CYCLE 1, 2 and 3 STUDY SCHEMA FOR IL-2 TREATED PATIENTS**

| Test/Assessment/Sample | Pre-cycle IL-2 (1) | D1 | D2 | D3 | D4 | D5 | D8(6)* | D29(6) |
| --- | --- | --- | --- | --- | --- | --- | --- | --- |
|  |  |  |  |  |  |  |  |  |
| SC IL-2 dosing |  | X | X | X | X | X |  |  |
| Toxicity/ adverse events(2) |  | X | X | X | X | X | X | X |
| Vital signs/ Karnofsky Performance Status | X |  |  |  |  |  |  | X |
| Physical examination(3) | X |  |  |  |  |  | X | X |
| CBC with differential and platelets(5) | X |  |  |  |  | X(4) |  | X |
| Serum chemistries(5) | X |  |  |  |  | X(4) |  | X |
| Pregnancy test-women only (5) | X |  |  |  |  |  |  |  |
| Flow cytometry | X |  |  |  |  |  |  | X |
| Plasma virology | X |  |  |  |  |  | X | X |
| Whole Blood for PBMC | X |  |  |  |  |  |  |  |

(1) All safety, virological and immunological laboratories must be performed within 96 hours prior to dosing.

(1) The results of all safety evaluations must be known before therapy may commence.

(2) Patients will document adverse experiences on diary cards on an ongoing basis.

(3) A complete physical exam will be performed prior to cycle 1. Thereafter physical exams will be symptom directed or as medically indicated.

(4) Can be obtained on day 4 or 5.

(5) Obtain during pre-therapy visit and immediately prior to dosing for each cycle.

(6) May be±5 days.

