**APPENDIX E. GUIDELINES FOR IL-2 DOSE REDUCTION**

The toxicities on the following table require IL-2 dose modification. A cycle in which such a toxicity occurs will be held until the toxicity is considered, in the opinion of the principal investigator, to no longer be dose-limiting.

The guidelines below are minimum recommendations and the decision to stop, dose-modify and/or restart study drug should be based on the clinical judgement of the principle investigator in discussion, as appropriate, with other investigators and/or the IND sponsors.

*** All Grade 4 toxicities as defined in Appendix D require that study drug be held until the toxicity decreases in severity to < Grade 2. Guidelines for the management of toxicities shaded in Appendix D (those toxicities which may require that study drug be held before Grade 4 severity occurs) are described below.**

| **HEMATOLOGY** | **HOLD IL-2 FOR:** | **CONSIDER RESTARTING**  **IL-2 FOR:** |
| --- | --- | --- |
| Hemoglobin | < 7.9 g/dL OR  < 79 g/L OR  < 4.92 mmol/L | > 9.4 g/dL OR  > 94 g/L OR  > 5.83 mmol/L |
| Platelets | < 50,000/mm3 OR  < 50 /G/L* | > 50,000/mm3 OR  > 50 /G/L* |
| Prothrombin Time (PT) | >1.5 X ULN | < 1.25 X ULN |
| PTT | >2.33 X ULN | <1.66 X ULN |
| *G = X 109 |  |  |

| **CHEMISTRIES** | **HOLD IL-2 FOR:** | **CONSIDER RESTARTING**  **IL-2 FOR:** |
| --- | --- | --- |
| SODIUM |  |  |
| Hyponatremia | < 129 meq/L **OR**  < 129 mmol/L | > 130 meq/L **OR**  > 130 mmol/L |
| POTASSIUM |  |  |
| Hypokalemia | <2.5 meq/L **OR**  <2.5 mmol/L | > 3.4 meq/L **OR**  > 3.4 mmol/L |
| CALCIUM - (corrected for albumin) |  |  |
| Hypocalcemia | < 7.0 mg/dL **OR**  < 1.74 mmol/L | > 7.0 mg/dL **OR**  >1.74 mmol/L |
| MAGNESIUM |  |  |
| Hypomagnesemia | <0.60 meq/L **OR**  <0.30 mmol/L | >0.9 meq/L **OR**  >0.45 mmol/L |
| **CHEMISTRIES** (con't.) | **HOLD IL-2 FOR:** | **CONSIDER RESTARTING**  **IL-2 FOR:** |
| GLUCOSE |  |  |
| Hypoglycemia | <40 mg/dL **OR**  <2.19 mmol/L | >64 mg/dL **OR**  >3.55 mmol/L |
| Hyperglycemia (nonfasting and no prior diabetes) | >300 **OR**  > 16.0 mmol/L | <200 mg/dL **OR**  < 11.1 mmol/L |
| CREATININE | >1.5 X ULN | <1.1 X ULN |

| **CARDIOVASCULAR** | **HOLD IL-2 FOR:** | **CONSIDER RESTARTING**  **IL-2 FOR:** |
| --- | --- | --- |
| CARDIAC ARRHYTHMIA | Asymptomatic; transient dysrhythmia, no Rx req | Resolution of dysrythmia |
| HYPERTENSION | Recurrent; chronic increase >20 mmHg, Rx req |  |

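### At any site with a creatinine ULN below 1.33 mg/dl, the entry limit and cycle 1 check can clear a patient who is already above the printed IL-2 hold limit

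*Protocol*

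**What the plan says.** Section VI.B, criterion (d) iii, requires "serum creatinine < 2.0 mg/dl" within 30 days of randomisation. In the same list AST and bilirubin are limited as multiples of ULN; creatinine is not.

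Section VIII.B.3 governs the start of cycle 1. The pre-cycle tests include chemistries, which Section VIII.B.1 defines to include creatinine. They must have "results known to be in keeping with study eligibility criteria before the patient is treated with IL-2". The limit for the first dose is therefore again 2.0 mg/dl.

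The creatinine row of Appendix E gives the hold limit and then the restart limit: "CREATININE | >1.5 X ULN | <1.1 X ULN". It makes no exception for a value that was raised before treatment. The introduction to that appendix says the listed toxicities require dose modification. It also calls the limits minimum recommendations and leaves the decision to the investigator's clinical judgement.

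After the pre-cycle sample, the next chemistries scheduled in Table 3 are the day 5 set, which footnote (4) qualifies: "Can be obtained on day 4 or 5".

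**The concern.** One laboratory value is judged on two scales. Eligibility and the cycle 1 check use mg/dl; the hold rule uses multiples of the local ULN. Section XVII has laboratories document their own normal ranges, so the relation between the two limits can differ by site. Where the local ULN is low enough, a patient can pass every printed check for the first dose with a creatinine at which Appendix E would hold the drug.

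Two things are at stake. The first is safety. Section II.A names creatinine elevation among the dose-limiting toxicities of intravenous IL-2, and Appendix F strongly recommends a nonsteroidal anti-inflammatory alongside treatment. The pre-cycle sample is the last scheduled chemistry before day 4 or 5.

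The second is how tolerance is recorded. If the value has not moved by day 4 or 5, it meets the hold criterion. If the investigator then treats it as dose-limiting, Section VII.C.1 starts the next cycle at a lower dose. A pre-existing value could then appear as IL-2 toxicity in a study whose first stated objective is safety and tolerance.

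**Working it through.** The protocol states no derived figure on this point, so the check is a direct comparison of limits.

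**Inputs.** Entry and cycle 1 limit: creatinine below 2.0 mg/dl (Sections VI.B and VIII.B.3). Hold limit: above 1.5 × ULN; restart guide: below 1.1 × ULN (Appendix E). Site ULN: not given; assumed here to lie between 1.0 and 1.4 mg/dl.

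**When the limits cross.** An eligible value C < 2.0 exceeds the hold limit if C > 1.5 × ULN. Such values exist only if 1.5 × ULN < 2.0, that is ULN < 2.0/1.5 = 1.333 mg/dl.

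**Width of the band** = 2.0 − 1.5 × ULN, in mg/dl:

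| Assumed ULN | Hold above | Restart below | Band width |
| --- | --- | --- | --- |
| 1.0 | 1.50 | 1.10 | 0.50 |
| 1.1 | 1.65 | 1.21 | 0.35 |
| 1.2 | 1.80 | 1.32 | 0.20 |
| 1.3 | 1.95 | 1.43 | 0.05 |
| 1.4 | 2.10 | 1.54 | none |

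**An illustration.** Take an assumed ULN of 1.2 and a stable creatinine of 1.9 mg/dl. The patient is eligible (1.9 < 2.0) and passes the cycle 1 check. The value is also above the hold limit (1.9 > 1.80). Once held, the patient meets the restart guide only below 1.32 mg/dl, a fall of more than 1.9 − 1.32 = 0.58 mg/dl from the patient's own baseline.

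**Doses before the next scheduled chemistry.** A full cycle is 2 × 5 = 10 doses. With two doses on each complete day, 2 × 3 = 6 have been given before a day 4 sample and 2 × 4 = 8 before a day 5 sample.

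**Do other entry laboratories cross their hold limits?** Three of the entry laboratory values have a row in Appendix E.
- Hemoglobin: entry is "hemoglobin > 11.0 g/dl" and the hold row begins "Hemoglobin | < 7.9 g/dL OR", a margin of 11.0 − 7.9 = 3.1 g/dL.
- Platelets: entry is "platelet count > 50000 cells/mm3" and the hold is below 50,000/mm3. The limits meet without overlapping.
- Creatinine: the only one of the three that can cross, and the only one expressed on different scales in the two places.

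**The case against.** The strongest reply is that the two limits do different jobs. Section VIII.B.3 says what governs the first dose: eligibility. Appendix E deals with toxicities that occur in a cycle, and with decisions to stop, modify or restart. Section XI.A defines an adverse event as a change in the patient, and a stable pre-dose creatinine is not a change. This stands. A reader might infer that the protocol contradicts itself, or compels dosing of someone it says must be held; the text does not support that. Section VIII.B.3 sets a necessary condition, not an order to dose. Clinical judgement (Section VII.C.1, Appendix E) and exclusion (k) leave the investigator free to withhold treatment.

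A reader might also infer that cycles 2 and 3 have no numeric creatinine limit, because Table 3 footnote (1) says only "The results of all safety evaluations must be known before therapy may commence". That does not follow either. By then the patient has received IL-2, so a raised creatinine can be handled as a toxicity under Section VII.C.1 and Appendix E, and Section VII.D.3 expressly allows a cycle to be delayed for IL-2 toxicity.

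It is also fair to say that creatinine is not the only Grade 2 value allowed at entry. AST below 4.9 × ULN, bilirubin below 2 × ULN and platelets just above 50,000/mm3 all reach Grade 2 in Appendix D. The creatinine limit may therefore be a deliberate tolerance. But AST and bilirubin have no Appendix E row, and platelets do not cross theirs, so this does not explain an entry limit above the hold limit.

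Finally, other safeguards exist. Cycle 1 should be given by a health professional (Section VIII.C.1), and extra safety tests are allowed (Section VIII.A). Appendix F calls for daily phone contact, urine-output measurement and medical evaluation of low output, and makes the higher indomethacin dose conditional on adequate renal function. These lower the risk but do not align the two limits.

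**Conclusion.** The concern holds as a minor safety-threshold mismatch confined to entry and cycle 1. At any site with a ULN below 1.333 mg/dl, a patient can be eligible and cleared for the first dose with creatinine already above the printed hold limit. If the value is unchanged at day 4 or 5, it meets the hold criterion and could be recorded as IL-2 toxicity.

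The size rests on an assumed ULN. The band runs from 0.50 mg/dl at ULN 1.0 to 0.05 at 1.3, and is absent from 1.333. How many of the 24 IL-2 patients would fall in it cannot be derived from the protocol; among asymptomatic patients it is probably few and may be none. Whether an unchanged value is in fact held or counted as toxicity depends on investigator judgement. Sample size, power and the CD4+ and HIV-RNA endpoints are unaffected.

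**What to change.** Restate criterion (d) iii in Section VI.B as creatinine at or below 1.5 × site ULN **and** below 2.0 mg/dl. Because Section VIII.B.3 refers back to the eligibility criteria, the new limit carries into the cycle 1 check without further wording. The highest admissible value then never exceeds 1.5 × ULN, so the overlap is zero at every ULN. Keeping the absolute limit prevents the change from loosening entry where ULN is above 1.333 mg/dl.

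The cost is an amendment to one criterion, with ethics review, and the loss of a rare patient with raised baseline creatinine. One matter remains: a patient who enters between 1.1 and 1.5 × ULN and is later held can meet the printed restart guide only by falling below baseline. Restarting such a patient would still need investigator judgement, which Appendix E already allows.

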### C. Exclusion criteria

a) prior IL-2 therapy.

b) prior or current use of any approved or experimental antiretroviral drug.

c) concurrent malignancy other than mucocutaneous Kaposi sarcoma or malignancy treated within the past 5 years.

d) any concurrent or history of AIDS defining illness (CPCRA appendix B).

e) use of systemic corticosteroids, chemotherapy or experimental cytotoxic drugs within four weeks prior to study therapy.

f) use of any agent approved or experimental with clinically significant immunomodulatory effects.

g) any CNS abnormality that requires treatment with anti-seizure medication.

h) patients with current or historical CrohnÕs disease, psoriasis or other autoimmune/inflammatory diseases with potentially life threatening complications.

i) pregnant or lactating women.

j) occasional or habitual use of recreational drugs/alcohol that in the opinion of the principal investigator would affect patient safety and/or compliance.

k) patients with any serious psychiatric, medical and/or cognitive disturbance or illness that in the opinion of the principal investigator may affect safety, compliance or ability to provide written informed consent.

# VII. TREATMENT PROCEDURES

Treatment must only be administered by one of the institutions identified as an investigational site in this protocol.

### A. Product description

Information on formulation, toxicities, stability and storage of interleukin-2 (aldesleukin, Proleukinâ) can be found in the Investigators Brochure.

Refer to Appendix C for information on reconstitution of interleukin-2.

Information on formulation, toxicities, dosing, stability and storage of antiretroviral drugs can be found on the package inserts for licensed therapies as provided.

### B. General considerations

Patients will be randomly assigned to receive trial medication in accordance with the schedule summarized in Table 2.

**Table 2. Randomization schedule and treatment assignments**

| TREATMENT ARM | RECRUITMENT (n) | STUDY DRUGS |
| --- | --- | --- |
| Control Group | 12 | no therapy |
| SC IL-2 | 12  12 | 4.5 MIU bid  7.5 MIU bid |

IL-2 will be delivered by twice daily subcutaneous injection for 5 days every 8 weeks. A cycle of therapy is defined as five days of IL-2 plus a further seven weeks.

### C. Dose modification

### 1. IL-2 Dose Modifications for Management of Toxicities

Adverse events will be graded according to the modified DAIDS/CPCRA Toxicity Table (Appendix D) used in association with the patientÕs clinical presentation. adverse events which may be dose-limiting are delineated by shaded boxes. The decision to dose-modify will be based on the clinical judgment of the principal investigator in discussion, as appropriate, with other investigators and/or the IND Sponsors. Patients who do not meet objective criteria for a dose-limiting adverse event but who find the side-effects intolerable, may be dose-modified according to the schedules described below.

Adverse events which in the InvestigatorÕs opinion are not IL-2 related but are delineated as dose-limiting may be discussed with the IND Sponsors. All adverse events must be reported in the case report forms regardless of the InvestigatorÕs assessment of their relationship to the drug.

The minimum dose that can be delivered under this protocol is 1.5 MIU q12h. The maximum dose will be 7.5 MIU q12h.

Recipients of IL-2 who develop toxicities will be managed as medically appropriate for the signs and symptoms of the toxicity. If the event or events are felt, in the opinion of the principal investigator to be dose-limiting, that cycle of therapy will be held until:

1. the DLT is no longer considered dose-limiting clinically, and

2. Grade 4 toxicities require that study drug be held until the toxicity decreases in severity to < Grade 2. Those toxicities which may require that study drug be held before Grade 4 occurs are shown shaded in Appendix D; IL-2 dose reduction guidelines for these shaded toxicities are given in Appendix E.

For the remainder of a cycle in which a DLT occurs, the patient may have their dose reduced by 1.5 MIU/dose. Dosing will continue to be delivered on a q12h schedule. Patients who require more than two dose modifications in a cycle of therapy will have that cycle of treatment terminated. Thus patients may be dose reduced to 6.0 MIU/dose and then to 4.5 MIU/dose during their first cycle of treatment if that cycle had commenced at 7.5 MIU/dose.

Patients who, during a cycle of therapy require dose modifications will have the subsequent cycles initiated at a dose below the level that gave rise to the dose limiting toxicity during the previous cycle. Subsequent dose reductions will occur, as necessary, in decrements of 1.5 MIU/dose delivered on a q12h schedule. Accordingly, patients can be dose-reduced in a step wise fashion from 7.5 MIU/dose to 4.5 MIU/dose to 1.5 MIU/dose. Patients who do not tolerate 1.5 MIU/dose will have IL-2 stopped.

The rationale for dose modification will be noted clearly in the case report forms. The maximum duration of dosing will be 5 days and will not be extended for doses missed due to management of toxicities.

If a patient previously dose-reduced completes a treatment cycle without toxicity then escalation of IL-2 dose at next cycle may occur by an increment of 1.5 MIU/dose.

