# IX. STUDY WITHDRAWAL

### A. Early termination of therapy

Patients will have their study therapy withdrawn if any of the following events occur:

i) withdrawal of consent to participate.

ii) termination of the study.

iii) pregnancy.

iv) a medically significant, grade IV toxicity occurs that is attributable to study therapy.

v) the patient experiences dose-limiting toxicities at the minimal permissible dose for this protocol (1.5 MIU q12h for 5 days every eight weeks).

vi) any event, other than those allowed that delays the commencement of an IL-2 treatment cycle by more than eight weeks.

vii) malignancy requiring systemic therapy.

viii) patient non-compliance.

ix) the principal investigator believes it is in the best interests of the patient.

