### APPENDIX C. INSTRUCTIONS FOR RECONSTITUTION OF IL-2 FOR ADMINISTRATION

**RECONSTITUTION OF IL-2**

The following information applies to dosage preparation for the Interleukin-2 (IL-2) formulation dispensed for this protocol only. The vials each contain a total of **21.6** million international units (MIU) of interleukin-2, and are labelled as Ò**SC RIL-2 Injection**Ó. To prepare single injectable doses at each of these dose levels, reconstitute with **sterile water** and withdraw the respective volumes as follows:

| Dose  (MIU) | Volume  sterile H2O (ml) | Final  concentration | Volume  per dose (ml) |
| --- | --- | --- | --- |
|  |  |  |  |
| **1.5** | **2.5** | **8.64MIU/ml** | **0.17** |
|  |  |  |  |
| **4.5** | **2.5** | **8.64MIU/ml** | **0.52** |
|  |  |  |  |
| **7.5** | **2.5** | **8.64MIU/ml** | **0.87** |
|  |  |  |  |
|  |  |  |  |

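### One sentence on between-cycle IL-2 dose reduction implies steps of 3.0 MIU where the rule says 1.5 MIU, Appendix C has no line for two doses on the 1.5 MIU ladder, and the grade 4 hold is not tied to the grade IV withdrawal rule

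*Protocol*

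**What the plan says.** **Dose steps (Protocol VII.C.1).** Within a cycle: "For the remainder of a cycle in which a DLT occurs, the patient may have their dose reduced by 1.5 MIU/dose". The limit is: "Patients who require more than two dose modifications in a cycle of therapy will have that cycle of treatment terminated". The illustration is: "Thus patients may be dose reduced to 6.0 MIU/dose and then to 4.5 MIU/dose during their first cycle of treatment", for a cycle begun at 7.5.

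For later cycles, the starting dose must lie below the level that caused the dose-limiting toxicity (DLT), and then: "Subsequent dose reductions will occur, as necessary, in decrements of 1.5 MIU/dose delivered on a q12h schedule". The next sentence, worded as a consequence, is: "patients can be dose-reduced in a step wise fashion from 7.5 MIU/dose to 4.5 MIU/dose to 1.5 MIU/dose". IL-2 is stopped in patients who do not tolerate 1.5 MIU/dose. Re-escalation after a toxicity-free cycle is by 1.5 MIU/dose.

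**Preparation (Appendix C).** The sheet is introduced with "To prepare single injectable doses at each of these dose levels" and has lines for 1.5, 4.5 and 7.5 MIU only. It also states the final concentration, 8.64 MIU/ml.

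**Grade 4 events.** VII.C.1 says: "Grade 4 toxicities require that study drug be held until the toxicity decreases in severity to < Grade 2". Appendices D and E repeat this for all grade 4 toxicities. IX.A lists the events for which study therapy will be withdrawn. Item (iv) is: "a medically significant, grade IV toxicity occurs that is attributable to study therapy".

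**The concern.** A sentence offered as the consequence of a 1.5 MIU rule describes steps twice that size. A site setting the next cycle's starting dose can find support in the same paragraph for either. The choice affects how quickly a patient reaches the dose at which further intolerance ends IL-2. Safety and tolerance of IL-2 is a primary objective, and each IL-2 arm has 12 patients. Doses received and stops for intolerance could therefore partly reflect which sentence a site followed.

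The preparation sheet matters because VII.C.1 itself names 6.0 MIU as a dose to be given, and later cycles may be self-administered. The grade 4 wording matters because a reader of VII.C.1 or the appendices alone would not learn that some grade 4 events require withdrawal.

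**Working it through.** **1. Step sizes.** Inputs: the two sequences in VII.C.1.
- Worked example: 7.5 − 6.0 = 1.5 and 6.0 − 4.5 = 1.5. This reproduces the stated step.
- Later sequence: 7.5 − 4.5 = 3.0 and 4.5 − 1.5 = 3.0. This does not reproduce the stated 1.5.

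**2. Reductions needed to reach the 1.5 MIU floor**, as (start − 1.5) / step:

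| Start | Step 1.5 | Step 3.0 |
|---|---|---|
| 7.5 MIU | 6.0 / 1.5 = 4 | 6.0 / 3.0 = 2 |
| 4.5 MIU | 3.0 / 1.5 = 2 | 3.0 / 3.0 = 1 |

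With one reduction per DLT, IL-2 stops at the DLT that follows arrival at the floor. That is the fifth against the third from 7.5, and the third against the second from 4.5.

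**3. Where the difference can arise.** Within a cycle the text fixes two reductions from 7.5 at 4.5, so there is no conflict there. Between cycles, take a patient starting at 7.5 with one DLT, at the starting dose, in each of cycles 1 and 2 (an assumed course). Cycle 3 starts at 7.5 − 2 × 1.5 = 4.5 under one reading and 7.5 − 2 × 3.0 = 1.5 under the other. Over a full cycle of 5 days × 2 doses = 10 doses, that is 10 × 4.5 = 45 against 10 × 1.5 = 15 MIU.

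**4. Appendix C.** The printed figures are correct: 21.6 / 2.5 = 8.64 MIU/ml, and 1.5, 4.5 and 7.5 divided by 8.64 give 0.174, 0.521 and 0.868 ml, matching 0.17, 0.52 and 0.87. Steps of 1.5 from 7.5 give 7.5, 6.0, 4.5, 3.0 and 1.5, and two of these five levels (6.0 and 3.0) have no line. Adopting 3.0 MIU steps for reductions between cycles would not by itself remove the gap, because re-escalation by 1.5 takes 4.5 to 6.0 and 1.5 to 3.0.

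**5. Grade 4 rules side by side.** VII.C.1 and Appendices D and E hold grade 4 events until below grade 2, with no exception and no reference to IX.A. IX.A(iv) requires withdrawal for events that are both medically significant and attributable, and does not say which grade IV events are medically significant. Restarting after a grade 4 value is contemplated in at least one place: the Appendix E hold level for hypomagnesemia (<0.60 meq/L) is the grade 4 threshold of Appendix D (<0.6 meq/L), and the same row gives a level (>0.9 meq/L) for considering a restart.

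**6. Sample size.** With 24 against 12 patients, SD 150 and difference 150, the standard error is 150 × √(1/24 + 1/12) = 53.0. Then 150 / 53.0 = 2.83 and power is Φ(2.83 − 1.96) = 80.7%, in line with the stated 80%. The 0.7 log calculation has the same ratio and gives the same result. No dose step enters either.

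**The case against.** The 1.5 MIU step appears four times: two rules, one example and the re-escalation increment. Only one sentence departs from it, and that sentence is permissive. It also has a coherent reading. DLTs at 7.5 and 6.0 in cycle 1 lead to a cycle 2 start of 4.5, and DLTs at 4.5 and 3.0 in cycle 2 lead to a cycle 3 start of 1.5. On that view 7.5, 4.5 and 1.5 are the starting doses of three cycles under maximum reduction. This is possible, but the text does not say it, and it gives no answer for a patient with a single DLT in a cycle.

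The objection does narrow the point. A reader might infer that the dose after any two reductions is ambiguous three-fold. It is not, because within a cycle the result is stated. A reader might also infer that the unlisted doses cannot be prepared. They can, since the concentration is printed and a volume follows by one division; and 3.0 MIU is implied by the step, not named.

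On grade 4, a reader might infer that the protocol orders both resumption and withdrawal for every attributable event. The documents do not support that. IX.A(iv) carries two qualifiers and can be read as a narrower rule on top of the general hold. A hold does not exclude later withdrawal, no text requires dosing to resume, and Appendix E leaves stopping and restarting to investigator judgement. What stands is the missing link and the undefined subset.

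Finally, the primary endpoints are CD4+ and HIV-RNA changes, with efficacy analysed by intention to treat across all IL-2 doses. That limits the statistical consequence but does not remove the bearing on the safety and tolerability objective.

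**Conclusion.** The inconsistency in VII.C.1 is real and confined to reductions between cycles. If the last sequence is taken as the between-cycle ladder, the floor is reached in two reductions instead of four from 7.5 MIU, and in one instead of two from 4.5 MIU. The 45 against 15 MIU contrast holds only for the assumed course of one DLT in each of the first two cycles from a 7.5 MIU start. The documents give no rate of dose reduction for this regimen, so the number of patients affected cannot be derived.

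The Appendix C omission is a real gap of modest practical effect. This assumes that the blank rows in the extracted table are spacing and not lost dose lines. The grade 4 point is secondary: an unlinked general rule and narrower rule, with the boundary between them undefined. Sample size and power do not change.

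**What to change.** - Reconcile the statements in VII.C.1 so that one reduction sequence is given within and between cycles, including the next starting dose after a single DLT.
- Give every dose on that sequence, and every dose reachable by re-escalation, a line in Appendix C.
- Cross-refer VII.C.1 and Appendices D and E to IX.A(iv), and make clear which grade 4 events are held and which lead to withdrawal.

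The choice of sequence and of grade 4 rule belongs to the sponsor and investigators; this review does not favour one. The cost is a protocol clarification and a revised preparation sheet, with no added patients, visits or tests.
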